### **Subject identification and recruitment:**

Subjects will be recruited through the Child and Adolescent General Outpatient Clinic, the Child Day-Treatment Program, and the Psychopharmacology Clinic in the Semel Institute. The Outpatient Clinic sees ~4000 children/year, ~ 5% of whom have PAE. Subjects will also be recruited from the UCLA Division of General Pediatrics at Mattel Children's Hospital, which sees 13,000 children/year. In addition to General Pediatrics, the Division of Genetics serves patients and families at risk for birth defects, developmental disabilities, and hereditary disorders. ~10% of children in these clinics have PAE. Beyond UCLA, we will recruit from practitioner referrals, schools, and the community using flyer posted at YMCAs, afterschool programs, barber and beauty shops. We also recruit from UCLA, FASD United, and FASD parent support websites. Social media will notify families of the study. We will use GoogleAds. We expect to enroll 30 patients (24 post-attrition) over 2 years.

### **Study Assessments**

#### **Screening and Eligibility Assessments:**

**Screening.** Swanson, Nolan and Pelham (SNAP-IV) Rating Scale (Bussing et al. 2008)—This is a long-standing, very widely used scale with good validity and reliability for detecting ADHD and quantifying ADHD symptom severity in children and young adults. It is administered by a clinician or researcher to parents. Children enrolled in our study must have confirmed PAE with a diagnosis of ADHD as part of their presentation (this is very common). In our study the Study Coordinator or a trained Research Assistant will administer the SNAP-IV during telephone screening to a parent or guardian of each prospective child with PAE. Purpose is to detect potential ADHD in the child and to screen out children with negligible ADHD symptoms. The SNAP-IV is also used, together with other instruments, to establish a diagnosis of ADHD during the eligibility visit.

**Diagnosis of ADHD.** MINI KID Parent Version. The MINI KID Parent Version refers to the parent version of the Mini International Neuropsychiatric Interview for Children and Adolescents (MINI-KID), a structured diagnostic interview used to assess various mental health disorders in children and adolescents from 6 to 17 years by asking questions directly to the child's parent, providing insight into their observations of the child's behavior and potential symptoms, allowing for a more comprehensive evaluation compared to just interviewing the child alone. Responses to the MINI-KID are binary (yes/no), indicating the presence or absence of a psychiatric disorder. The test uses branching loci where further questions are asked only if the initial screening questions indicate a potential diagnosis. The MINI-KID has previously demonstrated strong psychometric properties in clinical and general populations (Duncan et al. 2018, Sheehan et al. 2010). When tested during its initial development, researchers found the MINI reliability was excellent on interrater measures and very good on retest measures.

**PAE Physical Examination (Part of PAE Assessment)**—A Clinician Investigator or trained delegate conducts a physical of the child including measurement of height and weight, head circumference, and palpebral fissure lengths, as well as evaluation of upper lip and nasal philtrum and further assessments. Purpose is to gather evidence relevant to making a diagnosis of an FASD (fetal alcohol syndrome, partial fetal alcohol syndrome, or alcohol-related neurodevelopmental disorder). A diagnosis is required to rule-in subjects for the study. Thus, this is a detailed exam that can lead to a diagnosis of an FASD, including fetal alcohol syndrome (FAS), partial fetal alcohol syndrome (pFAS), or alcohol-related

neurodevelopmental disorder (ARND). We have recently demonstrated that non-FASD specialist child psychologists can be trained to perform this examination reliably ([name] et al. 2022).

**Facial Photos**—The original approved protocol called for conventional 2D photography of each subject's face to help identify and document facial dysmorphia potential associated with PAE. We have now expanded this part of the PE Examination to include three 2D pictures and three 3D pictures of the face from the front, side, and at a ¾ angle. We have also done this in our recent study of PAE (NIAAA R01AA025066). There are established links between neurodevelopment and the FASD facial phenotype. Without prior knowledge of PAE, FAS diagnosis (Astley et al. 2004, Hoyme et al. 2016) relies on accurate identification of abnormal facial features, growth deficits and CNS problems. However, since the extent of facial abnormalities may be dose-dependent and more evident in severe cases or in older children, more effective detection and quantification of facial dysmorphology, especially for mild or moderate cases and at younger ages may be needed. Understanding how facial dysmorphology is associated with brain abnormalities could likewise inform diagnosis and provide opportunities for intervention. Further, if demonstrated as sufficiently sensitive, using more cost effective 2D rather than 3D facial imaging might provide a new level of accessibility for diagnosing FASD in at-risk populations. Here we propose to collect 2D and 3D facial photographs to assess the potential of computer-based dysmorphology in predicting responses to TNS treatment.

**Health Interview for Women (HIW; [name] & Kasari 2000), Health Interview for Adoptive and Foster Parents (HIAFP; Quattlebaum & [name] 2013)(Part of PAE Assessment)**-- Exposure to alcohol and other teratogens is assessed with the HIW or the HIAFP. These scales were developed by Co-I [name] and colleagues at UCLA and have been used routinely for many years here and elsewhere. The HIW and HIAFP are structured interviews measuring the child's PAE and prenatal exposures to caffeine, tobacco, marijuana, methamphetamine, cocaine, barbiturates, opioids, hallucinogens, anticonvulsants, antibiotics, and OTC painkillers. They are administered by a Clinician Investigator or trained delegate to the birth mother, foster parents, or other informant. Purpose is to rule-in children with sufficient *in utero* ethanol exposure to qualify for the study and to rule-out children with exposures to other teratogens that, in the opinion of a Clinician Investigator (Drs. [name] or [name]), have impact exceeding that of ethanol (very rare).

**Kaufman Brief Intelligence Test –Second Edition Revised (K-BIT-2)**-- The K-BIT-2 is a brief screening tool used to assess intellectual functioning in individuals from 4 to 90 years (Kaufman & Kaufman 2004). The KBIT-2 IQ Composite score is an estimate of general intellectual functioning standardized with a mean of 100 and a standard deviation of 15. The IQ Composite score has high internal consistency across ages 4 through 18 ( $M = 0.93$ ) with test-retest reliability of 0.88. The correlation between the IQ Composite score and the General Ability Index of the WISC-IV is 0.84. It is administered by a trained Research Assistant to the child. Purpose is to rule-out children with intellectual disability (ID; IQ <70).

**Pubertal Development Scale (PDS, Petersen et al. 1988)**—Given the long-observed secular trend towards earlier puberty in children and at the request of our NIAAA review panel, we will use the PDS to measure pubertal development. It is a physically non-invasive test. Given that most youth are unreliable completing this questionnaire, it is advised to administer the scale to parents. The PDS includes five items that ask about growth in height, body hair, and skin changes. The PDS also asks about breast development and menarche in females and deepening of voice and growth of hair on face for males. Participants rate each item on a 1 (barely started) to 4 (seems complete) scale. The PDS has demonstrated good internal consistency with Cronbach's  $\alpha$  ranging between 0.91 and 0.96 and high test-retest reliability (ICC=0.81–0.92). Pubertal stage will be used as a covariate in statistical analyses.

Pre-Exposure to MRI Scanner—In a mock MRI scanner, children are given relaxation and breath training, and training in keeping still. From a distance, children are also shown the real MRI scanner. Purposes are pre-exposure for relief of anxiety and to rule-out children with claustrophobia or poor compliance.

#### Pre-TNS (Treatment) Assessments:

Clinical Global Impression—Severity (CGI-S) and Clinician’s Global Impression—Improvement (CGI-I)(Guy 1976)—These extremely widely used, multiply validated 7-point scales assess initial severity and improvement in core symptoms of a chosen mental disorder (here ADHD) based on the clinician’s experience with typical patients. They are administered by a Clinician Investigator, in this case to the parent reporting on the child. The CGI-S is administered at intake. Purpose is to serve as one metric of pretreatment severity of ADHD-like symptoms of PAE. The CGI-I is administered after TNS treatment and at follow-up. Purpose is to serve as one metric of post-treatment change in severity of ADHD-like symptoms.

ADHD-IV-Rating Scale (ADHD-RS; DuPaul et al. 1998)—The ADHD-RS is a parent interview administered by a Clinician Investigator. It was the primary outcome in the clinical trials leading to FDA-clearance of TNS for unmedicated pediatric ADHD. We use it to assess severity of ADHD-like symptoms in children with PAE at baseline and after the TNS treatment regimen.

Conners 4 Parent Version (Conners 4 P; Conners 2022)— The Conners 3 Parent Version originally proposed for this study to measure symptoms of ADHD is no longer available and has been replaced with the Conners 4 Parent Version (Conners 4 P) which provides a comprehensive assessment of symptoms and impairments associated with ADHD and common co-occurring problems and disorders in children and youth aged 6 to 18 years. The Conners 4 P is an inclusive and standardized measure that builds on the strengths of the Conners Rating Scales. Now fully digital, it provides online scoring for better data visualization, easy inventory management, a digital manual, and printable forms. It addresses critical concerns with Conduct and Self-Harm items and a Sleep Problems indicator. It also evaluates new content areas and common co-occurring problems such as Emotional Dysregulation, Depressed Mood, and Anxious Thoughts. Finally, the Conners 4 P provides a more comprehensive picture of how a rater approaches completing the measure, using new and updated validity scales, the number of omitted items, and the average number of items completed per minute. The Conners 4 P has excellent internal consistency (median omega coefficient = 0.94), strong test-retest reliability (median  $r = 0.89$ ), and convergent validity (median  $r = 0.73$ ). The parent completes the Conners 4 P before and after treatment.

Behavior Rating Inventory of Executive Function (BRIEF II) (Gioia et al. 2000)—The BRIEF II is a validated assessment of executive functions for children and adolescents that is very widely used clinically and in research. It is administered to parents before and after treatment by a Study Researcher. It takes 10-15 min. We use it to assess severity of executive function symptoms in children with PAE at baseline and after the TNS treatment regimen.

NIH Toolbox (Gershon et al. 2010)—The NIH Toolbox is a multidimensional set of measures to assess neurological and behavioral function available for clinicians and researchers. It is a valid, reliable, brief, and state-of-the-art instrument. We administer only the Cognition and Emotional Control Batteries to our pediatric patients. The latter assess domains of the PAE behavioral phenotype in DSM-5. (The primary author of this section of the DSM-5 is Co-I [name].) The Cognition Battery yields Cognitive Function Composite, Fluid Cognition Composite (Dimensional Change Card Sort, Flanker Inhibitory

Control and Attention, Picture Sequence Memory, List Sorting, and Pattern Comparison measures), and Crystallized Cognition Composite (includes Picture Vocabulary and Reading Recognition measures) Scores. The Emotional Control Battery surveys Positive Affect, Emotional Support, Friendship, Loneliness, Perceived Rejection, Perceived Hostility, Self-Efficacy, Sadness, Perceived Stress, Fear, and Anger. The Toolbox is administered by the Study Coordinator to the child before and after the TNS treatment regimen. Purpose is to assess baseline and post-treatment changes in function in cognitive and emotional control domains.

Delis-Kaplan Executive Function System (D-KEFS) Verbal Fluency (Delis et al. 2001,2004)—Unpublished data from our recent study of PAE (NIAAA R01AA025066) show significantly inferior performance ( $p < 0.001-0.041$ ; effect sizes 0.4-1.2) on 7/9 tests of the D-KEFS Verbal Fluency assessment. This is consistent with many prior reports of verbal fluency deficits in PAE (Iosub et al. 2018, Kingdon et al. 2016, Kodituwakku et al. 2006, Kovács et al. 2023, Mattson & Riley 1999, Panczakiewicz et al. 2018, Rassmussen & Bisanz 2009, Schonfeld et al. 2001, Vaurio et al. 2008). There are indications that disability in verbal fluency is mediated by executive function deficits (Doyle et al. 2018). TNS, as mentioned elsewhere in this proposal, improves executive function deficits in children with ADHD. We will administer the D-KEFS Verbal Fluency assessment to determine whether TNS induces improvement in verbal fluency. The D-KEFS Verbal Fluency Test is comprised of three testing conditions: Letter Fluency, Category Fluency, and Category Switching. This test measures multiple aspects of verbal behavioral productivity and cognitive flexibility. It evaluates effectiveness of novel and semantic search strategies, and assesses flexibility in the implementation of semantic search strategies. The process approach enables further evaluation of self-monitoring of information search, as well as difficulties related to initiation and sustaining effort. There are three conditions in the Verbal Fluency test in which the examinee must say as many words as they can by letter, category, and category switching prompts. 1. The examinee says words beginning with a specified letter as quickly as possible; 2. The examinee is asked to say words belonging to a designated semantic category; and 3. The examinee must alternate between saying words from two different; semantic categories. The test will be administered by the Study Coordinator or SRA I to the child.

Test of Narrative Language-- A common Narrative Protocol in developmental research utilizes the wordless picture book *Frog, Where Are You?* (Mayer 1969; FWAY) to elicit narratives from children. The book illustrates a story in which a boy and dog set out to search for their missing pet frog, encountering numerous mishaps until they are reunited and return home. The story is fun, engaging, and provides material for the production of a rich narrative in 29 illustrated frames. The Protocol is designed to allow for the evaluation of the presence, correctness, and frequency of narrative elements such as plotline identification (main plot and digressions), thematic identification (Miles & Chapman 2002), mean length of utterance (MLU), as well as for a wide range of linguistic elements: morphological errors, use of complex syntax, complexity of narrative structure, and types and frequency of evaluative devices. The Protocol is commonly used to study language development in typically and non-typically developing populations, such as children with Down's Syndrome (Miles & Chapman 2002); specific language impairment, early focal brain injury, Williams syndrome (Reilly et al. 2004), and fetal alcohol syndrome disorders (FASD; Vega-Rodríguez et al. 2020).

**Procedure.** The in-person interview is conducted by two adult experimenters. One of them acts as a listener for the child. The other introduces the storybook, gives instructions to the child, and audio-records the stories that the child creates. The child is asked to watch a video of the picture book silently (<https://www.youtube.com/watch?v=BwDc3aOb-E0>). Next the experimenter asks the child to narrate the picture book as they watch the video a second time. Administration takes ~6-8 min, further reducible (Berman & Slobin 1994,2013) if subjects are tired or insufficiently engaged.

The Revised Child Anxiety and Depression Scale (RCADS) for youth 8-18 years, is a 47-item, youth self-report questionnaire with subscales including: separation anxiety disorder, social phobia, generalized anxiety disorder, panic

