#### Post-TNS (Treatment) Assessments:

Conners 4 P (see above)—The parent completes a final Conners 4 P at the end of treatment.

CGI-I (see above)-- A Clinician Investigator administers the CGI-I to the parent at the end of treatment.

ADHD-RS (see above)-- A Clinician Investigator administers the ADHD-RS to the parent at the end of treatment.

BRIEF II (see above)—A Study Researcher administers the BRIEF II to the parent at the end of treatment.

NIH Toolbox (see above)—The Study Coordinator administers the two Toolbox batteries to the child at the end of treatment.

Delis-Kaplan Executive Function System (D-KEFS) Verbal Fluency. As above.

Narrative. As above.

CDI 2. As above.

RCADS. As above.

ARI. As above.

MR Exam (see above)— Two Study Researchers and/or Research Assistants conduct an MRI session at the end of treatment.

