  6. Post-TNS Assessment in completers within 1 week of completing TNS; same assessments as Pre-TNS
    - a. Height, weight, and vitals of the child are taken
    - b. The CGI-I and the ADHD-RS are administered by a Clinician Investigator to measure baseline ADHD symptoms
    - c. The NIH Toolbox is administered by the Study Coordinator to probe the Cognition and Emotional Control behavioral domains
    - d. The BRIEF II is administered to measure executive functions
    - e. The Conners 4 is administered to measure inattention and impulsivity/hyperactivity
    - f. The D-KEFS Verbal Fluency battery is administered to the child
    - g. The Test of Narrative Language is administered by the Study Coordinator to assay language impairments
    - h. The CDI 2 is administered to assess depressive symptoms and possible suicidality as a withdrawal criterion
    - i. The RCADS is administered to assess anxiety and depression symptoms
    - j. The ARI is administered to assess irritability
    - k.
  7. Post-TNS MRI to be performed maximum 1 week after completing TNS treatment
  8. 4 weeks after completing TNS, patients undergo Follow-Up Assessment, consisting of the CGI-I and the ADHD-RS.

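### The narrative task may be shortened for a tired or disengaged child with no requirement to match the pre- and post-TNS visits, so change in its presence and frequency measures can be biased in either direction

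*Protocol*

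**What the plan says.** The Procedure paragraph of the Test of Narrative Language (Protocol, Pre-TNS (Treatment) Assessments) describes two viewings of a video of a wordless picture book. The first is silent. The child narrates during the second: "Next the experimenter asks the child to narrate the picture book as they watch the video a second time". The stories are audio-recorded. On length it says: "Administration takes ~6-8 min, further reducible (Berman & Slobin 1994,2013) if subjects are tired or insufficiently engaged".

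The same section says the book "provides material for the production of a rich narrative in 29 illustrated frames". The intended measures include "evaluation of the presence, correctness, and frequency of narrative elements" and "types and frequency of evaluative devices", together with mean length of utterance (MLU), morphological errors, complex syntax and complexity of narrative structure.

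The task is given at both visits. Post-TNS (Treatment) Assessments lists it as "Narrative. As above". Under Research Protocol, steps 3 and 6 carry the same line: "The Test of Narrative Language is administered by the Study Coordinator to assay language impairments". Step 6 calls for the same assessments as before treatment but says nothing about equal length.

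Specific Aims describes an open trial in a single cohort and counts better attention as part of a favourable response. Measurements names the ADHD-RS as primary and the CGI as secondary.

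**The concern.** Shortening is triggered by low engagement, in children who all have ADHD, and engagement is close to what TNS is expected to change. The amount of story a child narrates may therefore depend on a state that shifts between week 0 and week 5. A child cut short at week 0 and given the whole story at week 5 has more opportunity to produce plot elements and evaluative devices, with no change in language ability. The reverse pattern would hide a gain. Familiarity with the staff and setting at the second visit could act in the same direction as a treatment effect.

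With no control arm, nothing in the design separates the two explanations. At stake is the reading of pre-post change in the length-dependent narrative measures only.

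**Working it through.** The protocol gives no effect size, SD or error rate for this task, so there is no stated figure to reproduce. What follows is an illustration.

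**Inputs from the protocol.** Full story: 29 frames. Completers: 24 (Sample size). Visits compared: weeks 0 and 5 (Timeline).

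**Assumed inputs.** Shortening removes narrated frames. Output per frame is constant. A shortened child narrates k = 24, 20 or 15 frames. Between-child SD is 30% of the mean, the correlation between visits is 0.7, and there is no true change.

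**Step 1: one child shortened at week 0 only.** Material lost = 1 − k/29. Apparent gain = 29/k − 1.

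| k | Material lost | Apparent gain |
|---|---|---|
| 24 | 1 − 24/29 = 17% | 29/24 − 1 = 21% |
| 20 | 1 − 20/29 = 31% | 29/20 − 1 = 45% |
| 15 | 1 − 15/29 = 48% | 29/15 − 1 = 93% |

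A child shortened only at week 5 shows an apparent loss of 17%, 31% or 48%.

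**Step 2: shift in the group mean.** With share a shortened only at week 0 and share b only at week 5, the expected shift, as a fraction of the full-length mean, is (a − b)(1 − k/29). It depends on the difference between the visits, not on the total amount of shortening.

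- a = 25%, b = 0: 0.25 × 0.172 = 4.3%, 0.25 × 0.310 = 7.8%, 0.25 × 0.483 = 12.1%.
- a = 15%, b = 10%: 0.05 × the same factors = 0.9%, 1.6%, 2.4%.
- a = b: zero.

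**Step 3: false positives.** Two-sided 5% paired t-test, n = 24, 20,000 simulated trials per cell:

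| Share shortened (week 0 / week 5) | k = 24 | k = 20 | k = 15 |
|---|---|---|---|
| none | 5% | 5% | 5% |
| 25% / 0% | about 14% | about 28% | about 43% |
| 10% / 0% | about 6% | about 9% | about 12% |
| 15% / 10% | about 5% | about 6% | about 6% |
| 12.5% / 12.5% | 5% | 5% | 5% |

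**Step 4: cost when shortening is balanced.** If 25% are shortened at each visit, independently, the false-positive rate stays near 5%. Power for an assumed true gain of 15% falls from 86% to about 76%, 57% or 36% for k = 24, 20 or 15.

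**The case against.** Several counter-arguments have force.

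- **What is cut is not stated.** Only the administration time is called reducible. Dropping or trimming the silent first viewing would save time without removing any narrated frame, and the frame arithmetic would then not apply. This stands. The two visits would still differ in preview, but by an amount these figures do not describe.
- **The large error rates need one-sided shortening.** Tiredness can occur at either visit, the task is short, and eligibility requires a child able to comply with procedures. No figure in the protocol supports 25% shortened, let alone all at week 0. This stands, so the one-sided row is an upper scenario and not an expectation.
- **The simulated test is not the planned one.** Data Analysis plans a linear mixed model and applies FDR outside the a priori imaging regions. A stricter threshold would lower the rates: at p < 0.01, used only as an illustration, the 25%/0% row falls to about 4% to 18%.
- **Direction is mixed.** MLU is a ratio and largely escapes. Raw morphological errors would rise with a longer narrative and look like worsening. A reader might infer that better engagement after TNS guarantees an apparent language benefit; the protocol does not support that.
- **Scoring may be specified elsewhere.** Per-frame or per-utterance scoring can sit in an SAP or scoring manual, so its absence here is not a fault. The recordings should also allow much of the matching afterwards. That answers part of the point only, because the procedure decides what is collected and the protocol does not ask for shortening to be logged.

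**Conclusion.** The point holds as a minor one. The protocol makes task length depend on the child's state, at visits whose results are to be compared, without matching or logging it. If narrated frames are what is cut, presence and frequency measures partly reflect how much was administered, and their change can be biased upward or downward.

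The size cannot be established from the protocol. Under the assumptions above it runs from essentially no inflation, when shortening is balanced or nearly so, to about 43% false positives when a quarter of children are cut to 15 frames at week 0 only. In the balanced case the harm is lost precision.

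A reader might also infer that the trial's efficacy conclusion is in doubt. It is not: the ADHD-RS and CGI results do not depend on this task, and Project Summary leaves the rigorous efficacy test to a later sham-controlled phase.

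**What to change.** In the Procedure paragraph, replace the open-ended reduction with a fixed rule: every child receives the same segment, either the full story or one pre-set short version, in the same way at both visits, including the silent viewing. Log any departure and the frames narrated at each visit. If a child is nonetheless shortened at one visit, compare only the frames narrated at both, using the existing audio recordings.

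The cost is a sentence or two in the procedure, one field on the record form and one scoring rule. It adds no visit. The downside is slightly less material for children shortened at one visit. The change does not remove a rise that comes from an engaged child saying more per frame, so that explanation should remain in the interpretation.
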